## USE OF ADVANCED, NON-INVASIVE DIAGNOSTIC METHODOLOGY FOR EARLY DIAGNOSIS OF SKIN CANCER IN IMPROVING THERAPEUTIC AND ECONOMIC-MANAGEMENT OF CLINICAL PRACTICE.

### **Background and rationale:**

The clinical diagnosis of cutaneous melanoma is complex. The aim of this project is to assess the effectiveness of the systematic integration of reflectance confocal laser microscopy (RCM) into the skin neoplasms diagnostic/clinical pathway.

Two instruments will be assessed:

- fixed head RCM (VivaScope 1500), capable of producing a virtual, non-invasive skin cancer in-vivo biopsy
- manual RCM (VivaScope 3000), for rapid screening of patients at high risk of melanoma for especially for early diagnosis of thin melanomas.

The evaluation of the cost-utility ratio of the device integration will be calculated based on a model specifically designed, developed and tested based on study data, within the network of the 3 collaborating hospitals (in a single Italian Region). The aim is to therefore evaluate whether the proposed skin cancer triage system is useful for reducing waiting lists and costs related to surgery and histopathology.

Skin neoplasms are the most common cancers in humans and represent substantial social costs for diagnosis and treatment. Due to the difficulty in arriving to a diagnosis based on clinical and dermoscopic evaluation only, a ratio of about 30 benign lesions excised for every melanoma identified has been calculated. RCM allows a non-invasive virtual biopsy of the tumor and a more accurate diagnosis thanks to the visualization of the skin lesion at a cytological resolution level. However, the advantage in clinical practice for patients and in economic terms of the implementation of this non-invasive technique as a pre-surgical diagnostic step has not yet been demonstrated. RCM may lead to the early diagnosis of skin tumors otherwise unable to be diagnosed in clinical and dermoscopy evaluations, potentially offsetting the enormous costs of treating advanced disease and considerably reducing the number of unnecessary excisions thus, representing a substantial economic advantage for health care.

RCM is a rapid, inexpensive and single-operator tool which will be added to the diagnostic triage. The main objective of the project is to assess the impact of the systematic application of RCM in a skin cancer triage, in terms of the number of unnecessary excisions, histopathological examinations and overall health costs.

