### **Design and description of the study**

This is a prospective randomized 2-arm study (performed in 3 hospitals). Consecutive patients with at least 1 lesion suspicious of melanoma (following clinical and dermoscopy evaluation) will be enrolled. Patients will be randomized to the standard therapeutical care ("Clinical and dermoscopy evaluation only") or standard therapeutical care + RCM integration ("RCM evaluation + clinical and dermoscopy evaluation") following identification of a suspicious lesion during the standard therapeutical care.

The main objective is to evaluate the safety of the integration of RCM (diagnostic identification of melanomas) and cost-effectiveness in terms of the comparison of the number of excisions needed to identify 1 melanoma (including the follow-up period). A cost-utility model will be developed to quantify the impact of the proposed triage system on health care costs and diagnostic effectiveness. This model will be tested on the study population.

Patients will be selected consecutively among patients with suspected skin cancer.

Randomization will be allocated at a 1:1 ratio and patients will be allocated to the “RCM evaluation + clinical and dermoscopy evaluation” or “Clinical and dermoscopic evaluation only” following standard therapeutic care; patients allocated to “Clinical and dermoscopic evaluation only” will likely require immediate biopsy for diagnosis, whereas clinicians of patients allocated to the “RCM evaluation + clinical and dermoscopy evaluation” can decide based on RCM evaluation whether to excise the lesion or refer the patient to subsequent digital follow up. Lesions referred to follow-up will be monitored for at least 6 months, and excised if significant changes are observed on dermoscopy.

In detail, the therapeutic-diagnostic pathway for each study arm are as follows:

a) "RCM evaluation + clinical and dermoscopy evaluation": following routine therapeutic care (clinical-dermoscopic examinations) clinicians of patients with suspicious lesions (at least one major or minor clinical and / or dermoscopic criterion for malignancy, as per inclusion / exclusion criteria) will be able to evaluate the lesions with RCM. A clinical decision (removal or digital dermoscopic follow-up) will be made based on the RCM evaluation.

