b) "Clinical and dermoscopic evaluation only": following routine therapeutic care (clinical-dermoscopic examinations) clinicians of patients with suspicious lesions (at least one major or minor clinical and / or dermoscopic criterion for malignancy, as per inclusion / exclusion criteria), will make a clinical decision (removal or digital dermoscopic follow-up) without RCM evaluation.

Each participating center will be responsible for its own case history and clinical decisions. Each center will take care of the collection and storage of data. At interim analysis (18 months) collected data and preliminary results will be evaluated collectively and discussed. The investigators at the participating centers have high-level therapeutic-diagnostic pathways in place, as documented by the numerous publications produced by these centers, however, in case of significant discrepancies among the interim clinical performance data, or if requested by individual investigators, some cases may be evaluated independently by other investigators in order to verify diagnostic agreement. These cases may derive either from direct indications from the investigators or randomly selected from the collected cases.

Images will be anonymized and only essential clinical data (sex / age, any significant present or past pathologies) will be provided to the other evaluators.

The definition of the head / neck lesion subset is as follows:

1. Malignant macules with histological diagnosis of melanoma;
2. Benign macules with histological diagnosis of actinic keratoses, solar lentigos, lichen planus-like keratosis, seborrheic keratoses, freckles and junctional / compound / dermal nevi;
3. Benign macules not subjected to biopsy and with clear and defined parameters of clinical, dermoscopic and confocal microscopy benignity;

The main outcome will be the rate of malignant lesions identified within the "RCM evaluation + clinical and dermoscopy evaluation" compared to "Clinical and dermoscopic evaluation only" study arms.

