The differences in the frequency of diagnoses obtained in the two study groups will be calculated and compared using the X2 test (chi-square). As a measure of diagnostic efficiency, the NNE (Number Needed to Excise), corresponding to the ratio between malignant lesions and excised benign lesions, obtained in the two different arms, will be calculated. Kolmogorov-Smirnov two-sample Z-test will be used to compare the differences in NNE obtained in the 2 arms. The cost - utility model will be developed in collaboration with the University of Pavia, Department of Pharmacological Sciences, in order to quantify the economic impact on the National Health System.

The model will take into account the costs of treatment (surgery / drug), examination, follow-up visits, devices and histopathology evaluation. The model will be constructed considering two possible alternatives: surgical excision versus RCM examination of equivocal lesions. The model will be tested and adapted based on the real data obtained from the prospective study.

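### The economic model sets RCM against surgical excision, but the randomised control arm may also follow lesions up, so its savings may be overstated by an amount the protocol does not let one size

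*Protocol*

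**What the plan says.** The structure of the economic model is given in one sentence of Protocol, Statistical analysis: "The model will be constructed considering two possible alternatives: surgical excision versus RCM examination of equivocal lesions". The sentence before it lists the cost components: "The model will take into account the costs of treatment (surgery / drug), examination, follow-up visits, devices and histopathology evaluation". The sentence after it says that the model will be tried out on, and adjusted to, the trial's own data. It does not say whether the comparator itself may change.

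The arms are described under Design and description of the study. In the RCM arm, clinicians "can decide based on RCM evaluation whether to excise the lesion or refer the patient to subsequent digital follow up". In the control arm (item b), clinicians "will make a clinical decision (removal or digital dermoscopic follow-up) without RCM evaluation". Earlier in that section, control patients are expected to be ones who "will likely require immediate biopsy for diagnosis"; no percentage is attached.

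The type of economic analysis has several names. Background and rationale promises "The evaluation of the cost-utility ratio of the device integration". Design and description of the study says: "A cost-utility model will be developed to quantify the impact of the proposed triage system on health care costs and diagnostic effectiveness". Secondary Objectives and Statistical analysis speak of a cost-benefit or efficacy calculation.

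**The concern.** A trial-based economic model should compare what the trial compares. Here both randomised strategies have the same two exits, excision and digital follow-up, and differ only in whether RCM informs the choice. The model as worded puts RCM on one side and excision on the other. If it is built that way, every control lesion that was in fact followed up is costed as an excision, and its avoidance is credited to RCM.

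This matters because the cost-benefit of fewer unnecessary excisions is the first item under Principal Objective. The model is also meant to quantify the effect on the National Health System and to be published for use in other settings. A saving measured against a strategy that no arm follows would lack the support of the randomised comparison.

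**Working it through.** **The plan's own figure.** The only economic result stated is a possible saving of about €30,000 per 100,000 inhabitants per year (Expected results, possible problems and solutions). It cannot be reproduced, because the protocol gives no unit costs, lesion volumes, excision shares or control follow-up share. What follows is algebra with assumed inputs.

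**Definitions.** One immediate excision plus histology costs 1. For control lesions, f is the share sent to follow-up, c the cost of follow-up relative to excision, and g the share of followed lesions excised later, each at cost 1.

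- Non-RCM cost per lesion if all are excised: 1
- Control-arm cost per lesion as randomised: (1 − f) + f(c + g)
- Difference: 1 − (1 − f) − f(c + g) = f(1 − c − g)

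The cost of the RCM strategy cancels, so this difference is the excess saving whatever happens in the RCM arm. For the count of excisions, the same step gives 1 − [(1 − f) + fg] = f(1 − g).

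**Sign.** The excess saving is positive when f > 0 and c + g < 1. It is zero when f = 0 or c + g = 1 (for example c = 0.3, g = 0.7), and negative when c + g > 1.

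**Size under assumed inputs.** With c = 0.3 and g = 0, f = 5% gives 0.05 × 0.7 = 0.035, and f = 30% gives 0.30 × 0.7 = 0.21.

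**Could it change the conclusion?** Assume also that the RCM arm excises 70% of lesions, that none of its followed lesions is excised later, and that RCM costs 0.1 per lesion. The RCM strategy then costs 0.70 + 0.30 × 0.3 + 0.1 = 0.89. Against excision of all lesions, it avoids 30 excisions per 100 and saves 1 − 0.89 = 0.11 per lesion. Against the control arm as randomised:

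| f | Control cost | Excisions avoided per 100 | Saving per lesion |
|---|---|---|---|
| 0% | 1.000 | 30 | 0.11 |
| 5% | 0.965 | 25 | 0.075 |
| 10% | 0.930 | 20 | 0.04 |
| 20% | 0.860 | 10 | −0.03 |
| 30% | 0.790 | 0 | −0.10 |

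Under these assumptions the saving changes sign between f = 10% and f = 20%. The table shows sensitivity and is not an estimate.

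**The case against.** The strongest reply is that the sentence is a brief outline of a model still to be built. It shows no decision tree, follow-up visits are among the listed costs without being confined to the RCM side, and the protocol says the model will be adapted to the trial's data. Immediate biopsy is the expected course for controls, so f may be small and excision a workable approximation. Much of this stands. Adaptation could extend to the comparator, and nothing excludes it. But nothing provides for it either, and the one sentence that defines the alternatives names the wrong one.

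It is also fair that the direction of the cost bias depends on c + g. A partial answer is that the saving expected from less surgery and histopathology itself relies on moving lesions to follow-up being cheaper than excising them. That makes c + g < 1 plausible, although g could differ between the arms.

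The larger values of f in the table also sit badly with the target of over 30% fewer unnecessary excisions. At f = 20%, excisions fall from 80 to 70 per 100. If every malignant lesion is excised in both arms, the target requires 10/(80 − m) > 0.30, so more than 46.7 of every 100 lesions would have to be malignant.

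Two stronger readings are tempting. A reader might infer that the two descriptions of the control arm contradict each other. They do not: one states an expectation, the other the permitted options. A reader might also infer that the model has no effect measure because its listed inputs are all costs. That goes too far. The list is a list of costs, the design section names diagnostic effectiveness, and Secondary Objectives names unnecessary excisions and melanomas diagnosed. What the protocol does not name is a utility. That is a matter of labelling, and a utility source may be left to an analysis plan that is not shown.

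**Conclusion.** The mismatch holds as a matter of text: the model's stated non-RCM alternative is excision, whereas the randomised control strategy is excision or follow-up. The consequence is conditional. Avoided excisions may be overstated by f(1 − g) per lesion, and the saving by f(1 − c − g) in units of one excision plus histology.

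A reader might infer that savings are overstated as a fact, or by a definite multiple. Multiples are easy to produce. If the RCM arm excises 60%, f = 10% gives 40/30 = 1.3 and f = 30% gives 40/10 = 4.0. But every such share is assumed, later excisions are ignored, and these are ratios of excisions, not of costs. The documents support neither a definite multiple nor a definite direction for cost.

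Severity is moderate. Randomisation, enrolment, the clinical endpoints and their tests are unaffected, and the model can be restated from data already planned.

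**What to change.** In Statistical analysis, replace the two alternatives with the two randomised strategies: clinical and dermoscopic care leading to excision or follow-up, against the same care plus RCM leading to excision or follow-up. State that branch proportions, follow-up visits and later excisions are taken from each arm as randomised. Data collection already provides for recording each lesion's initial decision, the later decision for followed lesions, and histology after excision, so no new lesion-level item is needed for the branches.

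As a minor labelling change, call the analysis cost-effectiveness, expressed per unnecessary excision avoided and per melanoma diagnosed, unless a utility source is named.

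The cost is a rewritten sentence and one more model branch. The projected saving may turn out smaller.

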**Inclusion criteria:**

- 1) Adult patients (18-90 years) referred to the Dermatology departments of the collaborating centers.
- 2) Patients able to give consent to participate
- 3) Patients with at least 1 lesion with at least one major or minor clinical and / or dermoscopic criterion of suspicion of malignant tumor lesion (Friedman 1987; Argenziano 2002) identified during the clinical and dermoscopy evaluation.
- 4) Willingness to participate in the study and able to give written informed consent

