Sensitivity, specificity, diagnostic accuracy, odds ratios (OR) with the 95% confidence interval will be evaluated. Several algorithms will be developed for the diagnosis of lentigo maligna in consecutive head / neck injuries. In particular, the positive and negative predictive values for each individual parameter analyzed will be measured and the combination of parameters capable of increasing diagnostic accuracy and reducing the number of unnecessary excisions, will be identified.

RCM features will be systematically analyzed to distinguish lentigo maligna from benign facial lentigos.

The time required for the assessment of face / neck injuries will be calculated and compared within the two groups.

The subgroup of non-melanocytic malignant lesions should include consecutive cases defined as:

1. Carcinomatous neoformations with histological diagnosis of basal cell carcinoma
2. Carcinomatous neoformations with histological diagnosis of squamous cell carcinoma
3. Benign neoformations with histological diagnosis of actinic keratoses, solar lentigos, lichen planus-like keratosis, seborrheic keratoses, ephelides and junctional / compound / dermal nevi.
4. Benign neoformations not subjected to histological analysis and with clear and defined parameters of clinical, dermoscopic and RCM benignity.

The main result is to evaluate the rate of histologically confirmed, excised basal cell carcinomas detected in the "RCM evaluation + clinical and dermoscopy evaluation" compared to "Clinical and dermoscopic evaluation only" study arms.

Sensitivity, specificity, diagnostic accuracy, odds ratios (OR) with the 95% confidence interval will be evaluated. Finally, the differences between the time, technical and human resources required within the "RCM evaluation + clinical and dermoscopy evaluation" compared to "Clinical and dermoscopic evaluation only" study arms.

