### **Statistical analysis**

Randomization: the "sample" function of STATA 13 (STATA Corp. College Station, Texas 2014) will be used weekly to predetermine the allocation of the subjects, in an alternating random manner, into the two study arms.

In the Coordinating Center, an estimated 800 patients will be enrolled (a total of 400 cases per study arm).

Outcomes include diagnostic safety of the RCM tool (measured by the number of excisions in relation to the number of melanomas diagnosed), a cost-benefit / efficacy calculation (based on an economic-drug model developed within the studio).

The estimated number of delayed cancer diagnosis within the "RCM evaluation + clinical and dermoscopy evaluation" study group is less than 1%.

Study power calculation: The expected percentage of melanomas identified in the "Clinical and dermoscopic evaluation only" group is 7.3% (Carli P, De Giorgi V, Nardini P, Seidenari S, Pellacani G, Peris K, Piccolo D, Rubegni P, Perotti R. *Skin Cancer Day in Italy: tumor detection rate and pattern of referral of open access clinics in an intermediate melanoma risk population. Eur J Dermatol* 2003; 13: 76-79) and for the "RCM evaluation + clinical and dermoscopy evaluation" group is 14% (Guitera P, Pellacani G, Longo C, Seidenari S,

As outlined in literature, approximately 22.4% of patients with "atypical" lesions are sent for treatment in highly experienced centers, equipped with digital dermoscopy (Alarcon I, Carrera C, Palou J, Alos L, Malveyh J, Puig S. *Impact of in vivo reflectance confocal microscopy on the number needed to treat melanoma in doubtful lesions. Br J Dermatol.* 2014; 170: 802-8) therefore, the enrolment of at least 2375 patients is required. Each collaborating center will enroll about 800 subjects.

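### The entry population and the efficiency numerator are each stated in two ways (melanoma, or any malignancy), so the meaning of the main efficiency measure is not fixed

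*Protocol*

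**What the plan says.** **Who enters.** Protocol, Design and description of the study, opens with "Consecutive patients with at least 1 lesion suspicious of melanoma". A little later the same section says: "Patients will be selected consecutively among patients with suspected skin cancer". Inclusion criterion 3 requires at least one major or minor "criterion of suspicion of malignant tumor lesion". Both arm descriptions speak of criteria for malignancy and refer back to the eligibility list.

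**Which tumours are studied.** Background and rationale and Secondary Objectives both include the diagnosis of basal cell carcinoma. The design section adds: "The subgroup of non-melanocytic malignant lesions should include consecutive cases defined as", followed by basal and squamous cell carcinomas and two groups of benign lesions. For this subgroup the arms are compared on the "rate of histologically confirmed, excised basal cell carcinomas detected".

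**What is counted.** The main objective in the design section compares excisions needed per melanoma found. In Statistical analysis, diagnostic safety is "measured by the number of excisions in relation to the number of melanomas diagnosed", and the sample size rests on melanoma percentages of 7.3% and 14%. The same section then defines the NNE with all malignant lesions on one side and excised benign lesions on the other. The design section also names, as a main outcome, the share of lesions found malignant in each arm. That sentence follows the definition of the head/neck subset and may apply only there.

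**The concern.** A patient whose only lesion is a suspected basal cell carcinoma is outside the first sentence of the design section but appears to be inside criterion 3. The carcinoma aims need such patients. The melanoma planning rates and the excisions-per-melanoma measure make most sense without them.

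If they are enrolled, each correctly excised carcinoma adds one excision and no melanoma, so the main-objective measure scores a correct decision as waste. The NNE scores the same excision as a success. The same data can then give two different answers about efficiency, and the Protocol does not say which one carries the conclusion. If instead entry is restricted to melanoma suspects, the carcinoma comparison covers only carcinomas that resembled melanoma.

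The problem is hard to repair afterwards. Data collection lists the decision at the visit and the histology of excised lesions, but not the type of suspicion at entry. Lesions sent to follow-up have no histology unless they are excised later. Classifying lesions later from stored images would be classification after allocation.

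**Working it through.** **1. The Protocol's own figures.** Inputs from Statistical analysis: 7.3% vs 14% melanomas, power 80%, α = 0.05, total 532, then 2375. With 1:1 allocation and pooled variance,

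n per arm = [z(α)·√(2p̄(1−p̄)) + z(0.80)·√(p₁(1−p₁) + p₂(1−p₂))]² / (p₂ − p₁)², with p̄ = 0.1065.

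- One-sided: (1.645 × 0.436 + 0.842 × 0.434)² / 0.067² gives 262 per arm, 524 in total. This is close to 532.
- Two-sided: 332 per arm, 664 in total. The unstated sidedness is a separate matter.
- 532 / 0.224 = 2375, as stated.

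These figures use melanoma rates only; no carcinoma share enters them.

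**2. The two efficiency measures under wide entry.** The Protocol gives no carcinoma share, so the following are assumptions. A share q of lesions enters only for suspected carcinoma and contains no melanoma. A fraction c of these (50% or 80%) are carcinomas. Of the remaining lesions, 7.3% are melanomas. The control arm excises everything. RCM spares 30% of all benign lesions (the Protocol aims for more than 30% fewer unnecessary excisions) and misses no malignancy.

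Per lesion enrolled: melanomas m = 0.073(1 − q), carcinomas k = cq, benign b = 1 − m − k.

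- Excisions per melanoma: control 1/m, RCM (m + k + 0.7b)/m. The relative cut is 0.3b.
- NNE as defined: control (m + k)/b, RCM (m + k)/(0.7b). Read as benign excisions per malignancy, the RCM/control ratio is 0.70 whatever q and c are.

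| q | c | Excisions per melanoma, control | RCM | Cut | NNE (malignant/benign), control | RCM |
|---|---|---|---|---|---|---|
| 0 | – | 13.7 | 9.9 | 28% | 0.079 | 0.112 |
| 30% | 50% | 19.6 | 14.9 | 24% | 0.252 | 0.360 |
| 30% | 80% | 19.6 | 15.4 | 21% | 0.411 | 0.587 |
| 50% | 50% | 27.4 | 21.5 | 21% | 0.402 | 0.574 |
| 50% | 80% | 27.4 | 22.8 | 17% | 0.775 | 1.107 |

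The control value of excisions per melanoma doubles from 13.7 to 27.4 through case mix alone, with no change in diagnostic performance.

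**3. When the dilution disappears.** Let RCM spare a fraction x of the benign lesions among carcinoma suspects, and still 30% of the other benign lesions. The cut is 0.3 × 0.927 × (1 − q) + x(1 − c)q. It returns to 0.278 when x(1 − c) = 0.278. With c = 50% this is x = 0.56. With c = 80% it would need x above 1, so dilution remains.

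**4. Power.** This is a separate calculation that reads 7.3% and 14% as shares of all enrolled patients and multiplies both by (1 − q). Two-sided at 0.05, with 2375 patients (1187.5 per arm), power is 99% at q = 30% (5.1% vs 9.8%) and 95% at q = 50% (3.65% vs 7.0%). With only 532 analysed it would be 71% at q = 0 and 54% at q = 30%.

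**The case against.** Several points on the other side stand.

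- A reader might infer that the trial is judged on a melanoma-only yardstick. It is not: the NNE counts any malignancy, and so does the design section's main outcome, whatever its scope. The defect is a conflict between numerators.
- A reader might infer that carcinoma suspects can only dilute the effect. The Protocol's non-melanocytic subgroup includes benign lesions, some never submitted to histology because they looked benign on RCM. RCM may therefore spare excisions there too, and step 3 shows that dilution can vanish.
- A reader might infer bias between the arms. Randomisation is 1:1, so carcinoma suspects enter both arms. Case mix changes the level and meaning of the measure without systematically favouring one arm.
- A reader might infer a loss of power. At 2375 patients there is none that matters.
- A reader might infer that centres will enrol by different rules. The arm descriptions defer to the formal eligibility list, so the Protocol does not show this. How far the cited criteria reach beyond melanoma cannot be settled from the document.

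One might add that the choice of analysis sets can be left to the SAP. That is fair for analysis detail. It does not cover who is eligible, what the main objective counts, or a data item that must be recorded before allocation.

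**Conclusion.** The point holds as an inconsistency in two places: who may enter, and what the efficiency measure counts. Under wide entry the excisions-per-melanoma measure penalises correct carcinoma excisions and the NNE does not, so the efficiency conclusion depends on which is read.

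The size is illustrative only. A 28% cut becomes about 21–24% at a 30% share of carcinoma suspects and 17–21% at 50%. This holds if the control arm excises everything, RCM spares 30% of benign lesions of either kind, and 50–80% of carcinoma suspects are carcinomas. The shares are assumed, and dilution is not certain. What is at stake is the interpretation of the estimate; the documents support neither a claim of biased arms nor one of insufficient power at the stated enrolment.

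**What to change.** 1. Make the design section and inclusion criterion 3 state the same entry population. If the narrow one is chosen, say that the carcinoma comparison covers only carcinomas that raised suspicion of melanoma.
2. Give each measure one stated numerator throughout the design and statistical sections. Say whether the main outcome on malignant lesions applies to the whole trial or only to the head/neck subset.
3. If entry stays wide, record for each lesion, before allocation, whether it is melanoma-suspected or carcinoma-suspected only. Report melanoma rate and excisions per melanoma in the melanoma-suspected lesions, and an all-malignancy NNE separately.
4. State that an excision with histologically confirmed carcinoma is not an unnecessary excision.

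The cost is a few sentences and one extra column in the existing lesion file, filled in at the entry visit. The melanoma comparison will rest on somewhat fewer lesions than the total enrolled.
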